#### Primary Outcome

The primary end point will be the change score in metacognitive abilities, as measured by the Jr.MAI [47] calculated based on the change between baseline and the 3-month follow-up assessment. The score summarizes 18 items and evaluates metacognitive abilities, focusing on metacognitive knowledge and regulation. The score ranges between 18 and 90, with higher values indicating better metacognitive abilities. Research findings confirmed the validity of the Jr.MAI and demonstrated the reliability of the overall score with a Cronbach α of 0.87 [52]. The Jr.MAI will be assessed in all subgroups and both experimental groups (Mio-Training vs waiting control) before and after the training and waiting period and at 3-month follow-up.

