### Statistical Analysis

The sample size was calculated for the primary outcome measure (Jr.MAI total score) using G*Power 3: repeated measures ANOVA (within-between subjects interaction); small effect size (Cohen *f*^2^=0.25); α=.05, power=0.8; retest correlation=0.5. The resulting minimal sample size is 14 participants per experimental group (Mio-Training vs waiting control group), corresponding to n=28 per subgroup (healthy controls, children and adolescents with cancer, and children and adolescents with ADHD). To compensate for losses and dropouts, the sample size was defined as 40 participants per subgroup, with a total sample size across all 3 subgroups of 120.

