Statistical analyses will be conducted using RStudio (Posit PBC). The planned statistical analyses were developed in consultation with an experienced statistician. The level of significance is set at α=.05. Data will be tested for normal distribution. The primary analysis will follow an intention-to-treat approach using linear mixed-effects models to calculate 2-sided 95% CIs for the primary outcome (Jr.MAI total score). The mixed-effects model will contain the total score of the Jr.MAI, the time points (ie, baseline, 5-week follow-up, or 3-month follow-up, as a categorical variable), treatment allocation (ie, Mio-Training vs waiting control group), the baseline score of the Jr.MAI (to adjust for individual differences in baseline functioning and to improve statistical precision), and stratification factors as fixed effects. The primary effect of interest is the treatment allocation-by-time point interaction. Participant ID will be included as a random intercept. Secondary end points will be analyzed using the same method. A per-protocol analysis will be conducted as a sensitivity analysis using the same model structure restricted to adherent participants (≥80% intervention compliance). Additional sensitivity analyses will examine differences in slopes over time between groups. Subgroup analyses will investigate potential effect modification by sex and age via interaction terms (treatment×sex and treatment×age), with stratified results reported where appropriate. Missing data exceeding 5% will be handled using multiple imputation by chained equations (50 datasets), incorporating all baseline and outcome variables at all time points as predictors. Rubin’s rules [64] will be used for pooling estimates. Variables with more than 50% missing values will not be used for the imputation model. To address multiplicity arising from secondary and subgroup analyses, a false discovery rate correction will be applied where appropriate. The primary analysis will not be adjusted for multiplicity, as it is prespecified and confirmatory. Secondary and exploratory subgroup analyses (including sex and age interactions) will be interpreted with false discovery rate–adjusted *P* values to control for type I error inflation arising from multiple comparisons.

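### As written, the sex and age interaction terms leave out time, so in the described model they estimate a T1–T3 average and not modification of the 3-month effect

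*Protocol article*

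**What the plan says.** Under Primary Outcome, the end point is the Jr.MAI change score, "calculated based on the change between baseline and the 3-month follow-up assessment". The Statistical Analysis section then describes one linear mixed-effects model:

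- The outcome is the Jr.MAI total score.
- The fixed effects include "the time points (ie, baseline, 5-week follow-up, or 3-month follow-up, as a categorical variable"), treatment allocation, the stratification factors and "the baseline score of the Jr.MAI (to adjust for individual differences in baseline functioning and to improve statistical precision").
- "Participant ID will be included as a random intercept".
- "The primary effect of interest is the treatment allocation-by-time point interaction".

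For sex and age, the same section plans to look for "effect modification by sex and age via interaction terms (treatment×sex and treatment×age"). Time is not part of either term. No separate model, time point or contrast is given for these tests. Results by stratum are promised conditionally, where the authors judge them suitable. On status, the section says: "Secondary and exploratory subgroup analyses (including sex and age interactions) will be interpreted with false discovery rate–adjusted" P values.

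**The concern.** Baseline is a level of the time factor, so the training effect in this model is carried by treatment×time. Modification of that effect by sex or age is therefore carried by treatment×time×sex or treatment×time×age. A treatment×sex term without time asks something else: whether the arm difference, averaged over all three visits, differs between boys and girls. One of those visits precedes any training.

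The coefficient would naturally be reported as the difference in training effect between sexes or age groups, and it is not that quantity. Sex and age are the stratification factors of the randomisation, so readers are likely to look at these results. False discovery rate adjustment deals with the number of tests and does not change what each test estimates.

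**Working it through.** **The plan's own figure.** The article gives no figure for the sex and age tests. The nearest one is the sample size of 14 per arm, 28 per population, with "α=.05, power=0.8; retest correlation=0.5". For a repeated measures ANOVA within-between interaction, λ = f²·N·m/(1 − ρ), df1 = (k − 1)(m − 1) and df2 = (N − k)(m − 1). With k = 2 arms, m = 3 measurements and f = 0.25:

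- λ = 0.0625 × 28 × 3 / 0.5 = 10.5, df1 = 2, df2 = 52, power 0.812. N = 28 is reproduced.
- With m = 2 the same inputs give N = 34.

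The stated size thus fits three measurements, which agrees with baseline being one of the outcome occasions. (The article prints the effect size as f² = 0.25. Taken literally that gives N = 10 with m = 3, or 12 with m = 2. This does not bear on the present point.)

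**What the two-way term estimates.** Let dt be the difference between strata in the arm contrast at visit t. With complete, balanced data and a random intercept, a term that does not vary within participant is estimated from participant means over the visits. Hence

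treatment×sex = (d1 + d2 + d3)/3, with d1 = 0 in expectation by randomisation.

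The primary end point calls for d3. For unit modifications (d2, d3):

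- (1, 1): (0 + 1 + 1)/3 = 0.67
- (0, 1): 1/3 = 0.33
- (0.5, 1): 1.5/3 = 0.50
- (1, 0): 1/3 = 0.33, although d3 = 0

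For positive d3, (d2 + d3)/3 exceeds d3 whenever d2 > 2·d3, so overstatement is possible as well as understatement.

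**Check by simulation.** There were 100,000 simulated participants. The correlation of 0.5 is taken from the plan. The SD of 10 points and the modification of 6 points are assumptions, and the one-third weights do not depend on them. The fixed-effect structure was fitted with the baseline covariate.

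| Modification at T2, T3 | Two-way term, formula | Two-way term, fitted | Three-way term at T3, fitted | Two-way term, T2/T3 rows only: formula; fitted |
|---|---|---|---|---|
| 6, 6 | 4.0 | 4.09 | 6.21 | 6.0; 6.13 |
| 0, 6 | 2.0 | 1.95 | 6.00 | 3.0; 2.93 |
| 6, 0 | 2.0 | 1.97 | −0.02 | 3.0; 2.95 |

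The departures are simulation noise. For the three-way contrast, the change from baseline has variance 2 × 100 × (1 − 0.5) = 100. With 25,000 participants in each of four cells the standard error is √(4 × 100/25,000) = 0.126, so 6.21 is about 1.7 standard errors from 6. The last column shows that dropping the baseline rows gives the T2/T3 mean, which is still not d3.

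**Detection at n = 40.** This was a small mixed-model run with 150 replicates and an assumed modification of 10 points. The Monte Carlo standard error is about √(0.4 × 0.6/150) = 0.04. Rejection rates at the 5% level were:

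| Pattern | Two-way term | Three-way term at T3 | Baseline-adjusted T3 model |
|---|---|---|---|
| T2 and T3 | 0.62 | 0.40 | 0.47 |
| T3 only | 0.25 | 0.40 | 0.47 |

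Only these two patterns were completed. The two-way term detects more often in the first and less often in the second.

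**The case against.** The best reply is that the subgroup sentence does not name a model. Secondary end points and the per-protocol analysis are tied explicitly to the primary model, but the sex and age tests are not. Treatment×sex is also common shorthand for modification of whatever the treatment effect is, and in a model of the T1-to-T3 change score it would be the right term. A condensed article may leave the full list of terms to an analysis plan that is not shown. This stands to the extent that the model is inferred. However, no change-score model is described, and the section writes time into the primary interaction but leaves it out of the subgroup interactions. An analyst who codes the text literally gets the wrong estimand.

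A second reply is that baseline also appears as a covariate, so the outcome rows might be T2 and T3 only. The time factor is said to include baseline. Even on this reading, the term gives a T2/T3 average.

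A third reply is that the stated aims cover short-term as well as long-term efficacy, so a T3-only target is not the only reasonable one. That is fair as to the objectives, but the primary end point is fixed at 3 months, and an average that includes T1 serves neither aim.

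A fourth reply is that results by stratum may be reported anyway. Fitting the primary model within strata would show the T3 contrasts, but that promise is conditional and does not replace the interaction test.

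Two stronger readings are tempting. A reader might infer that the plan always understates modification; the T2-only pattern contradicts this. A reader might also infer that the two-way test always loses power; the n = 40 run contradicts that when modification is sustained.

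**Conclusion.** The point holds, conditionally on the subgroup tests using the one model that is described. In that model the named terms estimate (0 + d2 + d3)/3 and not d3. This is about two thirds of a sustained modification, one third of a T3-only modification, and a non-zero value when modification exists at T2 alone. The fault is the estimand. The direction of the error depends on a time pattern that is not known in advance.

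The weights assume complete, balanced data and comparable arms at baseline. The rejection rates rest further on the assumed SD and modification size and on few replicates, and serve only to show that power can move either way.

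The documents do not support the claim that the authors certainly intend this test, because shorthand remains possible. They also give no ground for doubting the primary analysis, whose treatment-by-time test is untouched by this point. Importance is modest: the analyses are exploratory and adjusted for multiplicity. The wording should still be corrected.

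**What to change.** State the model and the contrast for the sex and age tests, in one of two ways:

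- Add treatment×time×sex and treatment×time×age, with all lower-order terms, to the described model, and report the T3 contrast in each stratum with a 95% CI.
- Fit a model of the T3 score adjusted for baseline, with treatment×sex and treatment×age, and report the same stratum contrasts.

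Restricting the outcome to T2 and T3 is not enough unless the T3 contrast is also specified. If the present terms were meant as shorthand, saying so and naming the T3 contrast settles the matter. Keep the analyses exploratory and false discovery rate adjusted.

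The cost is wording only, and the Results section says that data analysis has not begun. The statistical price is a wider interval, and lower power than the averaged term if modification is sustained across T2 and T3.

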### Outcome Measures

Baseline characteristics (age, sex, and socioeconomic factors) and clinical characteristics will be assessed through clinical chart review and questionnaires.

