## Results

The project is funded from October 2024 to December 2027. Data collection for the study with the healthy controls started in October 2024 and ended in August 2025. Data collection for the study with the cancer survivors started in August 2025 and is expected to continue until the end of 2027, while the study with the children with ADHD began in October 2025 and is projected to end in September 2026.

Forty participants have been recruited and assessed in the healthy control group, 10 (25%) participants in the cancer survivor group, and 39 (97.5%) participants in the ADHD group. In total, 40 participants per subgroup will be recruited. Data analyses have not yet commenced. First results from the ADHD study are expected to be published in late 2026 or early 2027. The healthy control data will not be published as a separate study, except for the feasibility results, but will be analyzed in comparison with the ADHD and cancer survivor groups. As recruitment for the cancer survivor study is more challenging and is expected to continue until the end of 2027, the ADHD study will be analyzed and published first. Publications from the cancer survivor study are anticipated for early 2028.

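### The stated imputation model has too many predictors for a subgroup of 40 children and does not name treatment allocation

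*Protocol article*

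**What the plan says.** All of the following is in the protocol article.

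- **Trigger and method** (Statistical Analysis): "Missing data exceeding 5% will be handled using multiple imputation by chained equations (50 datasets").
- **Predictors** (same section): "incorporating all baseline and outcome variables at all time points as predictors".
- **Only stated reduction** (same section): "Variables with more than 50% missing values will not be used for the imputation model".
- **Size** (same section): the calculated minimum is 28 per subgroup, and "To compensate for losses and dropouts, the sample size was defined as 40 participants per subgroup".
- **Timing and comparison** (Results): "the ADHD study will be analyzed and published first", while the healthy control data "will be analyzed in comparison with the ADHD and cancer survivor groups".
- **Baseline data** (Outcome Measures): "Baseline characteristics (age, sex, and socioeconomic factors) and clinical characteristics will be assessed through clinical chart review and questionnaires".

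The primary effect in the analysis model is the interaction of allocation with time point. The imputation sentence does not mention allocation. It also does not say whether imputation runs within a subgroup, within a clinical group plus healthy controls, or across all 120 children.

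**The concern.** The article gives a definite rule for choosing predictors, so the rule can be tested against the data it would meet. Two separate problems appear.

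1. Table 1 lists many instruments, most of them repeated at two or three visits and some completed by two raters. Put together as predictors, they rival or exceed the number of children in a subgroup. A chained-equations regression with about as many coefficients as observations is unidentified or barely identified. The result then depends on what the software does by default, such as dropping variables or adding a ridge penalty.
2. An imputation model should contain the terms of the analysis model. If allocation is absent, imputed scores are drawn as if the arms did not differ, beyond what other predictors carry, and the contrast between arms shrinks.

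The intention-to-treat result on the Junior Metacognitive Awareness Inventory (Jr.MAI) would be affected in both cases.

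**Working it through.** **1. The plan's own figure.** With k = 2 arms, m = 3 visits, retest correlation 0.5 and f = 0.25, the noncentrality is f²·N·m/(1−ρ) = 0.0625 × 28 × 3 / 0.5 = 10.5 on (k−1)(m−1) = 2 and (N−k)(m−1) = 52 degrees of freedom. Power is 0.812, so N = 28 is reproduced. (It needs f = 0.25. The article prints f², which does not affect this point.) The margin from 28 to 40 allows for 12/40 = 30% loss.

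**2. Is the trigger likely to be met?** 5% of 40 is 2, so three children with a missing value (7.5%) exceed it. At most 37 then have an observed 3-month score.

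**3. Counting variables.** Inputs are Table 1 (rows × visits × raters), plus age, sex and one socioeconomic variable. Short- and long-term memory count as separate scores.

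- ADHD: IQ 1 + executive tests 4×2 + processing speed 2 + attention 2×2 + verbal memory 2×2 + visual memory 2×2 + motor 2×2 + Jr.MAI 3 + BRIEF 2×3 + Conners 3 + resources 3 + physical self-concept 3 = 45; +3 = **48**.
- Cancer: remove attention (4) and Conners (3), add fatigue 2×3: 45 − 7 + 6 = 44; +3 = **47**.
- Healthy: the cancer set plus four further motor tests × 2: 44 + 8 = 52; +3 = **55**.

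One score per memory test removes 4, giving 44, 43 and 51. For ADHD it is 42 if Conners is collected at T1 only, as the text says, rather than at all three visits, as Table 1 says. The range is therefore 42 to 55, before any clinical characteristic or subscale is added.

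Narrow count, primary and secondary outcomes only: Jr.MAI 3 + executive tests 8 + speed 2 + memory 4 to 8 + BRIEF 3 to 6 = 20 to 27. Adding IQ, age, sex and one socioeconomic variable gives **24 to 31**.

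**4. What is left to estimate the model.** With V variables, the regression for one of them has V − 1 predictors and an intercept, so V coefficients. Residual degrees of freedom are observed children minus V:

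| 3-month scores missing | Observed of 40 | V = 24 | V = 31 | V = 42 |
|---|---|---|---|---|
| 10% | 36 | 12 | 5 | −6 |
| 20% | 32 | 8 | 1 | −10 |
| 30% | 28 | 4 | −3 | −14 |

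**5. Instability by simulation.** Assumptions: 40 children (20 per arm), correlation 0.5 between visits, true standardised effect 0.5 at T3, 10, 20 or 30% of T3 scores missing completely at random, auxiliaries correlated 0.3 with baseline, Bayesian normal imputation with a tiny ridge, 20 imputations, Rubin pooling, 600 runs per scenario.

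- With allocation and about 42 other predictors, the empirical SD of the estimate is 0.35-0.50, against 0.29-0.33 for a short model (allocation and Jr.MAI at T1 and T2). The large model's median reported standard error is only 0.31-0.34, so it understates the real spread.
- A separate run under similar assumptions used 20 to 25 extra predictors, close to the narrow count, with 20-30% missing. The median standard error rose from about 0.31-0.34 to 0.47-0.80, that is, by 0.47/0.31 = 1.5 to 0.80/0.34 = 2.4 times.

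**6. Leaving allocation out (same simulation, short model).** Shrinkage is 1 minus the ratio of the two means.

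| Missing | Effect at T2 | With allocation | Without | Shrinkage |
|---|---|---|---|---|
| 10% | 0 | 0.512 | 0.456 | 11% |
| 10% | 0.5 | 0.500 | 0.470 | 6% |
| 20% | 0 | 0.496 | 0.391 | 21% |
| 20% | 0.5 | 0.494 | 0.429 | 13% |
| 30% | 0 | 0.507 | 0.349 | 31% |
| 30% | 0.5 | 0.504 | 0.409 | 19% |

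**7. Pooling.** ADHD plus healthy gives 80 children and 48 − 7 = 41 shared variables. Across all 120, instruments used in one population only are 80/120 = 67% missing and fall to the 50% rule. Fatigue is 40/120 = 33% missing, so it stays and would be imputed for ADHD children who were never asked. That leaves 41 + 6 = 47 variables for 120 children.

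**The case against.** The strongest reply has four parts.

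- **Allocation.** A reader might infer that the plan excludes allocation and so will bias the effect toward zero. The text does not support that. It is silent, and the arm is fixed at baseline, so it may be meant among the baseline variables. The list under Outcome Measures describes data from charts and questionnaires, where the arm would not appear. This objection stands: the pull toward zero is conditional.
- **Size of the pull.** A reader might also infer that the effect shrinks by the full fraction imputed. That is near the top of the range. It falls to 19% at 30% missing when the observed T2 score carries the effect. The 30% is an enrolment margin, not a forecast, and the article states no attrition rate.
- **The count.** More predictors than children is not certain on every reading. The narrow count of 24 to 31 is below 40, and counting every instrument with the fewest scores and one rater gives 39 for ADHD and 37 for cancer. This stands for the headline comparison, but the residual degrees of freedom above show that the narrow set is still too large.
- **Pooling.** It would be wrong to say that pooling cannot help: at 80 or 120 children the predictors no longer outnumber them. But the article does not say that it pools. It sets the sample size per subgroup and analyses ADHD before the cancer group is complete, so a 120-child set will not exist for that report.

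The simulated auxiliaries carry little information and the regression is a plain one, so the instability figures lean toward the adverse side.

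**Conclusion.** The point holds in a limited form. Applied within a subgroup of 40, the stated rule asks for about 42 to 55 variables, or 24 to 31 on the narrowest reasonable reading. Neither supports a stable imputation regression once a material share of 3-month scores is missing. The consequence is an unreliable estimate and standard error: inflated by about 1.5 to 2.4 times with 20 to 25 extra predictors at 20-30% missing, and understated with about 42.

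The silence on allocation is a separate gap. Its cost, if allocation were really omitted, is about 6-11% of the effect at 10% missing and 19-31% at 30%. Adding allocation removes that bias in the short model but does not cure the excess of predictors.

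The conclusion rests on imputation per subgroup and on assumed missingness, effect size and correlations, none of which the article gives. Near the 5% trigger both effects are small to moderate.

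**What to change.** Replace the predictor rule with one of two statements.

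- **Short imputation model.** Impute separately in each population, with allocation in the model (or by arm), Jr.MAI at T1, T2 and T3, age, sex, and a few auxiliaries named in advance, for example BRIEF self-rating at each visit. State the population in which imputation is run.
- **No imputation for the primary result.** Use the already planned linear mixed model, fitted by likelihood to all observed visits, as the primary analysis of Jr.MAI. It is valid for outcomes missing at random given the model. Keep the short imputation model as a sensitivity analysis.

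The cost is a sentence or two and less computing. The one downside is that fewer auxiliaries support the missing-at-random assumption. The article says that analyses have not begun, so the change can be made without knowledge of the results.

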### Safety and Monitoring

Although the intervention is considered low risk, safety monitoring procedures were implemented for all subgroups. Potential adverse events include tiredness, frustration, distress, muscle soreness, or overexertion during or after the training sessions. Adverse events are monitored throughout the study via participant self-report, caregiver feedback, and study team observations during assessments. All reported events are documented and reviewed by the study team on an ongoing basis. In case of any adverse reactions, training sessions are paused or discontinued as appropriate, and participants are referred for clinical evaluation if necessary.

